### Inclusion Criteria

The study will recruit patients with moderate to severe refractory back pain who have not had previous major lumbar spine surgery, are not candidates for back surgery as assessed by a spine surgeon, or decline surgery. Refractory pain was defined based on a published guideline^31^ as failing to reach treatment goals, which may be related to inadequate pain reduction or daily functioning, or intolerable adverse effects. The complete inclusion criteria are listed in Table 1. The inclusion criteria are designed to be pragmatic to mirror those of nonsurgical patients currently seen in the clinic for whom SCS is indicated. Patients are eligible for the study whether they have unilateral, bilateral, or no concomitant leg pain.

**Table 1 papr12945-tbl-0001:** Inclusion Criteria

Have been diagnosed with chronic, refractory*, * axial low back pain and are not a candidate for surgery based on a spine surgeon’s assessment Pain should have a predominant neuropathic component as per the investigator’s clinical assessment Have not had any surgery for back or leg pain, or any surgery resulting in back or leg pain Considering daily activity and rest, have average back pain intensity of ≥5 out of 10 cm on the VAS at enrollment Be on no or stable pain medications, as determined by the investigator, for at least 28 days prior to enrolling in this study Be 18 years of age or older at the time of enrollment Be willing and capable of giving informed consent Be willing and able to comply with study‐related requirements, procedures, and visits Be capable of subjective evaluation, able to read and understand written questionnaires in the local language, and able to read, understand, and sign the written inform consent

* Pain is defined as refractory, regardless of etiology, when conventional medical management has failed to reach treatment goals that may include adequate pain reduction and/or improvement in daily functioning or have resulted in intolerable adverse effects.

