### Participants

Patients will be recruited in 15 centers in the United States. In all centers, patients who have not obtained satisfactory results with CMM and have not had previous major lumbar surgery will be screened for eligibility by medical record review. Consent will be obtained from potential candidates and the following screening assessments will be performed: back and leg pain on the VAS, magnetic resonance imaging (MRI), x‐rays with or without flexion‐extension views if indicated, and surgical consultation. Inclusion requires a diagnosis of chronic axial low back pain with a neuropathic component. Candidates will complete the PainDETECT questionnaire for assessment of a neuropathic pain component.^32^ The PainDETECT questionnaire will be used to guide the investigators’ assessments, but the score will not be used to automatically exclude potential subjects since the literature is mixed in terms of validating its use in the detection of neuropathic back pain.^33^ Appropriate interventional procedures should have been tried prior to enrollment with continued refractory pain.^31^ All patients were required to have an MRI‐based diagnosis and spine surgical expert opinion that surgical intervention was not indicated. If all eligibility criteria are met, demographics and baseline assessments will be collected, and subjects will be randomized.

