### Data Management and Statistical Analysis

Descriptive statistics will be used to summarize all subject baseline and outcome data collected during the study. Continuous variables will be summarized using means, standard deviations, and ranges. Categorical variables will be summarized in frequency distributions.

Analysis populations defined for the study include intention‐to‐treat (ITT) and per protocol (PP). The ITT population includes all randomized subjects, while the PP population includes subjects who completed the visit corresponding to the endpoint being analyzed. Note that subjects who fail the temporary trial will be included in the ITT population for the high‐frequency stimulation at 10 kHz (HF10) + CMM arm.

The primary endpoint will be evaluated with a Fisher’s exact test comparing the percentage of subjects in each group who achieve a 50% improvement in their back pain VAS score at the primary efficacy assessment in the ITT population. The following secondary endpoints will be successively evaluated (hierarchical closed test approach) at study completion in the order shown with a 0.05 significance level for difference between groups in the PP population until statistical significance is not achieved.

The comparison between HF10 + CMM and CMM alone in terms of healthcare resource use (HRU) will be made based on doctor’s office visits, emergency room visits, or hospital stays, as well as on medical tests and procedures. Medication use (opioids and medication for CLBP), work status, health status (12‐Item Short Form Survey [SF‐12]), quality of life (EuroQol 5‐Dimension, 5‐Level Instrument [EQ‐5D‐5L]) will be used in the cost‐effectiveness analysis. The change from baseline to 6‐month follow‐up will be compared for CMM vs. HF10 + CMM for all these parameters. In addition, subjects can be used as their own control comparing HRU at baseline to HRU after baseline for the HF10 + CMM arm, or pre‐ and post‐crossover for those crossing over from the CMM to HF10 + CMM at 6 months. Parametric functions (eg, Weibull, Gompertz, etc.) will be used to extrapolate from 6‐month HRU to 1, 2, and 3 years out. HRU will be associated with direct medical costs using fee schedules, Medicare claims, and peer‐reviewed literature. Changes in EQ‐5D‐5L index scores will be used to assess changes in health status and the economic value of the addition of HF10 to CMM.

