Pain	Percentage change from baseline in back pain intensity (as assessed by the VAS) Percentage of subjects in each group who experience a back pain intensity VAS score of ≤3.0 cm for at least 6 months (remission definition)^36^ For subjects who have baseline leg pain VAS scores ≥ 5.0 cm, percentage change from baseline in leg pain intensity For subjects who have baseline leg pain VAS scores ≥ 5.0 cm, percentage of subjects in each group who experience a leg pain intensity VAS score of ≤3.0 cm for at least 6 months (remission definition)^36^ Changes in Short‐Form McGill Pain Questionnaire
Disability	Percentage change from baseline in ODI score comparing the treatment and control groups Proportion of subjects who experience at least a 10‐point reduction in the ODI score Change in proportion of subjects reporting <20 (minimally disabled) on the ODI total score
Quality of life	Health‐related quality of life evaluation comparing treatment and control groups as measured by the EuroQol 5‐Dimension, 5‐Level questionnaire Mental and physical health evaluation (12‐Item Short Form Survey) comparing treatment to control groups Measure of depression severity comparing treatment and control groups as measured by the Patient Health Questionnaire‐9
Global impression of change	Subject’s and clinician’s impressions of change in overall health condition in each group as measured by the Patient Global Impression of Change and Clinician Global Impression of Change questionnaires, respectively
Satisfaction	Assessment of subject's satisfaction with treatment in each group
Performance	Comparison of length of time to complete 50‐foot walk at fastest speed test
Sleep	Changes in sleep as determined by Pain and Sleep Questionnaire 3‐item index in each group
Work	Missed work days by subject or caregiver Change in subject’s work status in each group Percentage of subjects who have returned to work in each group
Medication	Change from baseline in opioid equivalent medication usage in the subpopulation prescribed opioids at baseline in each group^†^ Change in opioid side effects as measured by a Numerical Opioid Side Effect assessment tool in the subpopulation prescribed opioids at baseline in each group
Healthcare utilization	Between group comparison of number of office visits, emergency room visits, hospital admissions, and medical interventions during the months prior to enrollment and during study follow‐up

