Patient Health Questionnaire‐9^57^	Assessment of depression with chronic pain. Scores each of 9 criteria from 0 (not at all) to 3 (nearly every day). The maximum possible score = 27. Scores of greater than 5, 10, 15, and 20 represent, mild, moderate, moderately severe, and severe, respectively.	50% decline and a score less than 10^58^
Physical performance measure: the 50‐foot walk at fastest speed^59^, ^60^	Speed to walk 50 feet when instructed to walk at fastest safe speed	Minimum detectable change is 3.08 seconds based on the coefficient of variation^61^

MCID, minimum clinically important difference.

Quality of life measures (EQ‐5D‐5L, SF‐12), the depression module of the PHQ‐9, and patient satisfaction self‐reported outcome will provide a measure of how the therapy affects overall quality of life and mental health. Mental health is an important outcome because those suffering from chronic low back pain are 3 to 4 times more likely to suffer from depression than the general population.^37^

Opioids are widely prescribed for chronic low back pain, but there is little evidence for their efficacy in the long term.^8^ Prevalences of substance abuse disorders are as high as 43%, and prevalences of aberrant medication‐taking behaviors are as high as 24% in patients with CLBP who are prescribed opioids.^8^ Change in daily opioid use in terms of morphine equivalent dose will be assessed with a patient diary. These data will address whether 10‐kHz SCS can provide an alternative therapy to opioids, avoiding side effects and opioid addiction.

A tertiary objective is to assess the impact of the addition of 10‐kHz SCS therapy on HCU by the patient with NSRBP. This will be the first study to report a cost‐effectiveness outcome comparing 10‐kHz SCS + CMM to CMM in this patient group.

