### Limitations

Due to the nature of the treatment groups, it is not feasible to blind either the subjects or the clinical site personnel to treatment group assignment. Subjects randomized to 10‐kHz SCS + CMM will receive stimulation delivered through an implanted SCS system. The system requires the use of external components for programming and daily recharging, thus precluding subjects from being blinded to their treatment group.

The lack of blinding provides a potential for bias. In preparing the investigational plan, elements have been put in place to anticipate and minimize potential sources of bias.
The qualifications of each investigator and his or her ability to appropriately screen and treat subjects and to comply with investigational plan requirements will be reviewed before their participation in the trial.The study will be conducted under a common protocol at all study sites.The sponsor, investigators, and study participants will remain blinded to aggregated study results, except for recommendations made during a single, preplanned interim analysis.In order to minimize potential assessment bias, the subjects will receive standard instructions for completing the questionnaires.

One limitation of this study is the potential for a “nocebo effect,” since one arm of this study entails the continuation of the CMM treatment the patients have been receiving. But this effect is mitigated due to the regular care and assessment that the CMM arm group receives within the study. It is likely that some patients will achieve improved treatment results compared to previous CMM in this more intensive care scenario.

In addition, this pragmatic open‐label study is not designed to remove the effect of a subject’s expectations for the therapy or placebo effect. In the practice of real‐world chronic pain treatment, the placebo effect may be considered part of the therapy, “shaping the central nervous system toward pain relief,” since psychological factors are known to influence chronic pain management.^42^

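### The optional own-control comparisons of healthcare use measure total change over time, not the effect of adding 10-kHz SCS, and should be descriptive only

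*Protocol article*

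**What the plan says.** Healthcare use is a tertiary matter. Under Expected Outcomes of the Study the article writes "A tertiary objective is to assess the impact of the addition of" 10-kHz SCS on healthcare utilization.

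The section Data Management and Statistical Analysis first plans a randomized contrast: "The change from baseline to 6‐month follow‐up will be compared for CMM vs. HF10 + CMM for all these parameters". Table 5 agrees, listing the outcome as "Between group comparison of number of office visits, emergency room visits, hospital admissions, and medical interventions" before enrollment and during follow-up.

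The same section then adds, as an option, that "subjects can be used as their own control comparing HRU at baseline to HRU after baseline for the HF10 + CMM arm". The alternative is a comparison before and "post‐crossover for those crossing over from the CMM to HF10 + CMM at 6 months". The before-baseline comparison is named for the HF10 + CMM arm and not for the CMM arm. No caveat and no adjustment for a concurrent control is given.

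Other statements bear on what would happen without SCS:
- Inclusion Criteria (Table 1): subjects must "have average back pain intensity of ≥5 out of 10 cm on the VAS at enrollment".
- Crossover: a subject needs less than 50% back pain relief, documented dissatisfaction and investigator agreement.
- Sample Size Calculation: 36% of CMM subjects are assumed to respond.
- Limitations: "It is likely that some patients will achieve improved treatment results compared to previous CMM in this more intensive care scenario".

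**The concern.** A one-arm before-after contrast asks whether use changed. The objective asks whether adding SCS changed it. The two questions coincide only if use would have stayed flat without SCS, and the article does not expect patients on CMM alone to stay as they were. It assumes that more than a third of them reach the responder threshold, and it anticipates better results under study care than under their previous care. Subjects are also enrolled while their pain is above a threshold, which invites regression to the mean. Crossovers are chosen because their first six months went badly on relief and satisfaction.

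The word control invites a reader to treat the before period as the counterfactual. A fall in use in the SCS arm, or after crossover, could then be reported as a saving from SCS even if CMM subjects showed the same fall. Conversely, an implant-related rise in use could be read as a cost trend with nothing to set it against.

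**Working it through.** **The plan's own figure.** The article states no figure for the HRU analysis. It does state 98 per group for the primary endpoint (60% vs 36%, Fisher's exact test, two-sided 0.05, 90% power). This reproduces: the continuity-corrected formula gives 98, and exact Fisher power at 98 per group is 90.7%. I use 98 below only as a plausible number of subjects per arm.

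**What each contrast estimates.** Let τ be the effect of adding SCS on mean use, and δ the change that would occur anyway.
- Before-after change in the HF10 + CMM arm: τ + δ.
- Change in the CMM arm: δ.
- Randomized difference in change: (τ + δ) − δ = τ.

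The before-after test has null τ + δ = 0, which is the null of no SCS effect only if δ = 0. This part needs no numerical assumption.

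**Illustration of size under τ = 0.** The article gives no visit rates, dispersion or drift, so all of these are assumed. A subject has rate μ·g per period, where g is gamma with mean 1 and shape s, and counts are Poisson given g. Use falls by a fraction d in both arms.
- Mean fall = μd.
- Variance of change = μ(2 − d) + (μd)²/s.
- Standardized drift k = mean fall / SD of change.
- Rejection rate ≈ Φ(k√n − 1.96) + Φ(−k√n − 1.96), with n = 98.

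| μ | s | d | mean fall | variance | k | k√98 | rejection rate |
|---|---|---|---|---|---|---|---|
| 3 | 1.5 | 10% | 0.3 | 5.76 | 0.125 | 1.24 | 24% |
| 3 | 1.5 | 20% | 0.6 | 5.64 | 0.253 | 2.50 | 71% |
| 4 | 1.0 | 10% | 0.4 | 7.76 | 0.144 | 1.42 | 30% |
| 4 | 1.0 | 20% | 0.8 | 7.84 | 0.286 | 2.83 | 81% |
| 6 | 1.5 | 10% | 0.6 | 11.64 | 0.176 | 1.74 | 41% |
| 6 | 1.5 | 20% | 1.2 | 11.76 | 0.350 | 3.46 | 93% |

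Simulation of the same model agrees within a few percentage points. At μ = 4 it gave 29% and 82%, and its lowest value for μ = 3 was 23%. With d = 0 the before-after test rejects at about 5%, as it should. The randomized test of change rejected in 4% to 6% of trials in every scenario. With 50 subjects and μ = 4, the before-after rates are about 16% and 51%.

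**Crossover contrast, selection only.** Assume no drift and no SCS effect, with a mean of 4 visits per period. Take the worst 64% of 98 CMM subjects by severity in the first period (1 − 0.36, treating every assumed non-responder as crossing over). Let severity correlate 0.3 to 0.7 between periods and act on the log visit rate at 0.2 to 0.5 per SD. Selection alone then produces an apparent fall in use of 3% to 13%. It is significant in favor of SCS in 5% to 28% of trials, against a nominal 2.5% in that direction.

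**The case against.** The strongest reply is that the article already makes the randomized comparison the main one. It comes first, Table 5 repeats it, and the own-control look is introduced as something that can be done in addition, for a tertiary objective outside the primary test and the secondary hierarchy. The article attaches no null hypothesis, significance level or savings claim to it, so it could be meant as description. After crossover no intact randomized control remains, and the footnote to Table 5 openly limits 12-month analyses to within-group. All of this stands and limits the importance of the point. It does not make the contrast an answer to the question of adding SCS, and at 6 months a proper control arm is available.

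Three stronger readings are tempting and are not supported.
- **That the bias must favor SCS.** HRU includes tests and procedures, and the SCS arm undergoes a lead trial and possibly an implant after baseline. Table 2 also bars interventions within 30 days before enrollment, which can lower baseline use. The net direction is unknown.
- **That screening work-up inflates baseline use.** Under Participants, after consent, "the following screening assessments will be performed: back and leg pain on the VAS, magnetic resonance imaging (MRI" and other items including a surgical consultation are listed. The article does not say that these count as baseline HRU, and Table 5 refers to the months before enrollment.
- **That own-control results feed the economic model.** The article says that 6-month HRU is extrapolated. It does not say that the own-control estimate is the one used.

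**Conclusion.** The point holds in a limited form. The own-control and pre/post-crossover comparisons estimate total change over time, so neither a fall nor a rise in them can be attributed to adding SCS. That conclusion is structural.

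The illustrative size (roughly 23% to 93% false significance at 98 subjects for a shared 10% to 20% fall, against about 5% for the randomized contrast) depends on assumed visit rates, dispersion and drift, and on a paired test at 0.05 that the article does not specify. It shows sensitivity to drift; it does not show that this trial has such drift. The randomized 6-month HRU comparison and the primary and secondary endpoints are not affected.

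**What to change.** In Data Management and Statistical Analysis, state that any claim about the effect of adding SCS on HRU, any savings statement, and the HRU effect used in the cost-effectiveness analysis rest on the randomized 6-month difference in change (HF10 + CMM vs CMM). Label the before-after figures in the HF10 + CMM arm and the pre/post-crossover figures as descriptive, without tests or savings claims. Beside the HF10 + CMM before-after change, show the CMM arm's change over the same window.

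The cost is a few sentences and one further column in a table, with no new data or patients. What is lost is an inferential within-subject savings claim.

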### Sample Size Calculation

Assuming a 60% responder rate in the stimulation group (10‐kHz SCS + CMM) and 36% in the control group (CMM), a sample size of 98 subjects in each group is enough to detect a significant difference with a power of 90% and a 2‐sided type I error of 0.05. Assuming a 10% attrition rate, a total of 108 subjects per group need to be randomized.

The sample size computation is based on the 2‐sided Fisher’s exact test, used for comparing 2 independent proportions, following an equal allocation randomization ratio of 1:1.

Sites will be enrolling in the study a maximum of 54 subjects (25%) per site of the total number of study subjects (216 subjects).

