### Interim Analysis

A single interim analysis is planned for when approximately 40% of the planned study population reach the 3‐month primary endpoint. The objective of the interim analysis will be to assess the primary endpoint in order to potentially stop the study early for efficacy or futility, or to increase the sample size for the second part of the study. The overall alpha of 0.05 will be split so that the alpha required to reject the null hypothesis at both the interim and final analysis will be 0.025.

The interim analysis will be carried out by an unblinded independent third‐party statistician who will follow the above‐mentioned procedure and make a recommendation without disclosing interim analysis results or the conditional probability of success to the sponsor.

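### The stated 90% power assumes a two-sided 0.05 test, but the plan tests the primary endpoint only at 0.025; at that level 98 per group gives about 85%

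*Protocol article*

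**What the plan says.** The Sample Size Calculation section of the protocol article gives the planning inputs. "Assuming a 60% responder rate in the stimulation group" and "36% in the control group (CMM"), it claims that "a sample size of 98 subjects in each group is enough to detect a significant difference with a power of 90" percent. The error rate is a two-"sided type I error of 0.05", and the method is the two-sided Fisher's "exact test, used for comparing 2 independent proportions, following an equal allocation randomization ratio of 1:1". Attrition is then added: "Assuming a 10% attrition rate, a total of 108 subjects per group need to be randomized", which makes 216 in total.

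The Interim Analysis section plans one look at the primary endpoint, when about 40% of the planned population have reached 3 months. The look can stop the trial for efficacy or futility, or enlarge it. The overall 0.05 is split so that "the alpha required to reject the null hypothesis at both the interim and final analysis will be 0.025".

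The Trial Status section reports that the interim look included 101 subjects (43 and 58) and that enrolment closed at 211.

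**The concern.** The two sections use different levels for the same test. The sample size is justified at 0.05, yet the rejection rule is 0.025 at the interim and 0.025 again at the end. The sample size paragraph makes no allowance for the split. A stricter level at an unchanged sample size means lower power, so 90% cannot be right for the design as described.

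At stake is how the trial's sensitivity is presented. A reader who takes the paragraph at face value believes that the planned effect would be missed one time in ten. This is not a detail that a condensed article leaves to its full protocol: both levels are printed, and they do not fit together.

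**Working it through.** **Inputs.** Responder rates p1 = 0.60 and p2 = 0.36, 98 evaluable per group, 10% attrition, 1:1 allocation and two-sided Fisher's exact test (Sample Size Calculation). Level 0.025 at each look, first look at about 40% (Interim Analysis). Actual interim numbers 43 and 58, and 211 enrolled (Trial Status). I read the 0.025 as two-sided because it is half of an overall 0.05 that the sample size section calls two-sided.

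**Step 1: reproduce the plan's figure.** With d = p1 − p2 = 0.24 and mean rate 0.48, the uncorrected size per group is

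n = [z(α/2)·√(2·0.48·0.52) + z(β)·√(0.60·0.40 + 0.36·0.64)]² / d²

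At α = 0.05 and 90% power: (1.960·0.7065 + 1.2816·0.6859)² / 0.0576 = 88.97, so 89. The continuity correction, which approximates Fisher's test, is

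n′ = (n/4)·[1 + √(1 + 4/(n·d))]² = (88.97/4)·(1 + √1.1873)² = 97.1, so **98**. This is the plan's number.

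**Step 2: change only the level.** At α = 0.025, z(α/2) = 2.241. The same formulas give 105.3, so 106 uncorrected, and **114** with the correction.

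**Step 3: exact power.** For each pair of group sizes, all 2×2 tables were enumerated, the two-sided Fisher p-value computed for each, and the binomial probabilities of the rejecting tables summed.

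| Evaluable per group | Power at 0.05 | Power at 0.025 |
|---|---|---|
| 95 (211 × 0.9 = 189.9, halved) | 89.2% | 82.7% |
| 97 (108 × 0.9 = 97.2) | 90.3% | 84.2% |
| 98 (plan) | 90.7% | **84.9%** |
| 105 and 106 (all 211 with data) | 92.8% | 88.2% |
| 108 (all planned, no attrition) | 92.7% | 88.1% |
| 111 | 93.8% | 89.7% |
| 112 | 94.1% | **90.1%** |

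Fisher's test is discrete, so power moves in small jumps and a change of one subject can shift it by a point or more.

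**Step 4: credit the interim look.** Overall power = P(reject at interim) + P(no rejection at interim, then rejection at final), each look at 0.025.

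- 39 per group, then 98: 39.9% at the interim, **85.9%** overall.
- 43 and 58, then 95 per group: **84.1%** overall.
- 43 and 58, then 105 and 106: **89.0%** overall.
- 43 per group, then 108: 88.8% overall.

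**Step 5: the attrition step.** 98/0.90 = 108.9, which rounds up to 109. The plan's 108 matches 98 × 1.10 = 107.8. The difference is one subject per group, and 97 per group would still give 90.3% at 0.05, so this is only a rounding note.

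**The case against.** **The interim look could have enlarged the trial.** Power at a fixed 98 per group is then not the whole of the design. That is true of the design, but the sentence at issue claims 90% for 98 per group, and no increase was made. Futility stopping, which the look also allows, could only lower power.

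**The attrition margin may cover the gap.** It narrows it. With every one of the 211 subjects contributing 3-month data, power is 88.2%, or 89.0% with the interim look credited. This upper bound belongs in any fair account, but it is still short of 90%.

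**The final level is already stated.** This stands. The Interim Analysis section gives 0.025 for the final test, and the 0.05 in the Data Management and Statistical Analysis section concerns the secondary endpoints. A cross-reference is enough.

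**Two stronger readings are tempting and not supported.**

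- A reader might infer that the decision to stop enrolment because the trial was adequately powered rests on the 0.05 calculation. The Trial Status section attributes that recommendation to the interim results. The Interim Analysis section refers to a conditional probability of success, and the level used in it is not shown.
- A reader might count missing subjects as non-responders and put the chance of missing the effect near 20%: 54% versus 32.4% with 108 per group gives 79.8% at 0.025. No section states that rule. Missing Data mentions only multiple imputation as a sensitivity analysis. Part of that loss is also unrelated to the split, since the same scenario gives 86.8% at 0.05.

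**Conclusion.** The power statement is wrong as written. At the level that the plan actually uses, 98 evaluable per group gives about 85%, or about 86% with rejection at either look credited. That is 4 to 5 points below the stated 90%. For the 211 enrolled, the range is about 83–84% with 10% attrition to about 88–89% with complete data, so the chance of missing the planned effect is roughly 11% to 17%.

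These figures rest on the plan's own responder rates, on reading 0.025 as two-sided, and on no futility stop. They describe power at the planning stage and say nothing about the chance of success given the interim data.

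The matter is a modest misstatement to be corrected. Testing at 0.025 twice keeps the overall type I error within 0.05, and the endpoint, test and decision rule are unaffected.

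**What to change.** Keep enrolment closed. Restate the sample size paragraph along these lines: with a two-sided level of 0.025 at each of the two analyses, 98 evaluable subjects per group give about 85% power for 60% versus 36% by Fisher's exact test (about 86% counting rejection at either look); the 211 enrolled give about 83–84% with 10% attrition and at most about 88–89% with complete data. Refer there to the Interim Analysis section for the level of the final test. In the same edit, either correct 108 to 109 or note that 108 leaves about 97 evaluable.

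The cost is the rewording of one paragraph and a less favourable power figure. No subjects, visits or analyses are added.
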